## Abstract

**Background:**

Strong evidence suggests that maternal-infant skin-to-skin contact (SSC) is effective in reducing behavioural responses to pain. Given the multi-sensory benefits of SSC, it is highly likely that SSC provided during pain in early life may reduce pain-induced brain activity. The aim of this study is to examine the effect of SSC compared to 24% sucrose on pain-induced activity in the preterm infant brain during a medically required heel lance. Secondary objectives include determining (a) differences between behavioural pain response and noxious-related brain activity during heel lance and (b) rate of adverse events across groups.

**Methods:**

We will randomly assign 126 babies (32 to 36 completed weeks gestational age) admitted to the neonatal intensive care unit, and their mothers within the first seven days of age to receive (i) SSC plus sterile water and (ii) 24% oral sucrose. Each baby will receive a medically indicated heel lance, following a no treatment baseline period. The primary outcome is noxious-related brain activity measured using an electroencephalogram (EEG) pain-specific event-related potential. Secondary outcomes include pain intensity measured using a bio-behavioural infant pain assessment tool (Premature Infant Pain Profile-Revised) and rate of adverse events.

**Discussion:**

This will be the first clinical trial to compare the effect of SSC and 24% sucrose on pain-induced brain activity in the preterm infant brain during a clinical noxious stimulus, measured using EEG. Given the negative neurodevelopmental outcomes associated with unmanaged pain, it is imperative that preterm babies receive the most effective pain-reducing treatments to improve their health outcomes. Our findings will have important implications in informing optimal pain assessment and management in preterm infants.

**Trial registration:**

ClinicalTrials.gov NCT03745963. Registered on November 19, 2018.

## Administrative information

Note: the numbers in curly brackets in this protocol refer to SPIRIT checklist item numbers. The order of the items has been modified to group similar items (see http://www.equator-network.org/reporting-guidelines/spirit-2013-statement-defining-standard-protocol-items-for-clinical-trials/).

## Background and rationale {6a}

Humans in the last trimester of gestation are assumed to be in a pain-free environment in the womb. However, one in every ten babies worldwide is born preterm and often spends weeks in the neonatal intensive care unit (NICU) where they will undergo numerous painful procedures as part of their routine care [1–5]. A recent systematic review of epidemiological studies reported that preterm infants underwent a daily average of 12 painful procedures, with the majority receiving no interventions to alleviate pain [6]. These findings are consistent with a Canadian survey carried out by members of this research team, which indicated that higher exposure to painful procedures and lack of pain-relieving interventions were the most frequent in the youngest and sickest neonates [7]. At one time it was believed that preterm infants did not experience pain, but two decades of behavioural observation studies [8–11], as well as recent studies using near-infrared spectroscopy (NIRS) [12, 13], electroencephalography (EEG) [14–17], and functional magnetic resonance imaging (fMRI) [18] to document cortical responses to noxious stimuli provides compelling evidence that infants as young as 25 weeks gestational age experience pain. In addition to immediate deleterious physiological effects and suffering, untreated early pain has been associated with long term consequences in children, including cognitive [19, 20] and language deficits [21], motor delays [22, 23], behavioural problems [24], and poor executive functioning [24–26]. In addition to outcomes assessed through standardized measures, imaging studies have demonstrated decreased frontal and parietal brain width [27], and altered diffusion measures and functional connectivity in the temporal lobes [28] of infants highly exposed to pain.

### Sweet tasting solutions and non-pharmacological pain management in the NICU

While pharmacological interventions may appear to be a logical solution to minimize pain, they can be inadequate, unavailable, or impractical for the most common procedures such as heel lance, venipuncture, intravenous insertion, or intramuscular injection [29–31]. This is of significant concern, as together these procedures make up 94% of tissue-breaking painful exposures experienced by infants in hospital [32]. As such, we and others have examined the effectiveness of alternative interventions such as sweet tasting solutions (sucrose [33] or glucose [34]) and non-pharmacological strategies (skin-to-skin contact [35] (SSC), often referred to as kangaroo care, which is the upright ventral holding of a diaper clad baby on the bare chest of a mother or alternate care provider), non-nutritive sucking (pacifier) [36], or swaddling (bundling in a blanket) [36] to reduce neonatal pain response. There is now strong evidence from Cochrane and other systematic reviews that, based on bio-behavioural measures (physiological, facial, or body responses), oral sucrose [33] and non-sucrose sweet tasting solutions [34], as well as SSC [35], are the most effective methods to reduce pain associated with commonly performed needle-related and tissue-breaking procedures in preterm infants in the NICU. Despite this evidence, there remains little understanding of the effect of these interventions on nociceptive (i.e. pain-related) responses in the neonatal brain. Specifically, whether interventions used in clinical practice lead to modulation or blunting of noxious pain-related brain responses, or solely depresses the expression of behavioural responses (e.g. facial actions). A recent systematic review including 74 human studies (*n* = 7049) [33] has shown that intra-oral sucrose (currently considered standard of care for hospitalized infants) effectively reduces bio-behavioural responses of preterm infants undergoing procedural pain. Although widely practised, there is some evidence that brings the analgesic efficacy of sucrose into question. In one study by Slater [15], reported in the Lancet, sucrose decreased bio-behavioural pain scores in infants undergoing heel lance when compared to a no treatment control, however, sucrose did not significantly reduce the amplitude of a Noxious-related event-related potential measured using EEG, suggesting that its effects may be sedative in nature rather than analgesic [15]. These findings support concerns raised by Abbott and Guy [37], who demonstrated using a rat pup model that while behavioural response to pain was similar between rats that were administered morphine and pentobarbital, only morphine blunted the nociceptive pain specific response, demonstrating the difficulty in discerning between sedation and analgesia using solely bio-behavioural measures.

## Objectives {7}

The *primary objective* of this study is to characterize the effect of SSC condition compared to 24% oral sucrose on noxious-evoked brain activity in the preterm infant brain during a clinically required heel lance procedure.

*Secondary objectives* are to determine (a) differentiation between bio-behavioural pain response and noxious-related brain activity elicited by clinical heel lance; (b) frequency of adverse events between interventions across groups; and (c) maternal acceptability of study participation.

### Hypotheses

#### Primary

Infants randomized to the SSC condition, when compared to infants randomized to the 24% oral sucrose condition, will demonstrate a lower amplitude pain-specific event-related potential during a clinical (heel lance) noxious stimulus.

#### Secondary

Infants randomized to the SSC condition, when compared to infants randomized to the 24% oral sucrose, will demonstrate (a) less differentiation between bio-behavioural pain response and noxious-evoked pain activity elicited by clinical (heel lance) noxious stimulus and (b) fewer adverse events (i.e. episodes of choking, apnea, bradycardia, temperature instability, need for repeat heel lance or “rescue sucrose” doses).

## Trial design {8}

A single centre, single-blind, parallel randomized controlled two-arm trial superiority design, similar to our previous studies in this population[38], will be utilized. Infants will be randomized to (i) SSC or (ii) 24% oral sucrose where they will undergo a clinically required heel lance. All aspects of the study will undergo institutional ethical approval. No infant will undergo pain associated with a heel lance procedure without intervention as per recent recommendations [39].

## Methods: participants, interventions, and outcomes

### Study setting {9}

The study will be conducted in the NICU of the IWK Health in Halifax, Nova Scotia, a 40-bed tertiary level referral unit.

### Eligibility criteria {10}

Infants considered to be medically stable, whose parents have provided informed consent, and require a clinically indicated heel lance, will be recruited to participate. Infants delivered between 32 and 36 completed weeks gestational age (GA) at birth admitted to NICU whose parents can read and write English will be approached for inclusion within the first seven days of age. Determination of stability will be made in consultation with the attending neonatal staff. Exclusion criteria are major congenital anomalies, received or receiving opioids in the previous 24 h, immediate post-op surgical period (< 72 h), history of hypoxic-ischemic encephalopathy requiring cooling, and contraindication for sucrose administration (e.g. unable to swallow, paralysis) due to safety concerns or inability to assess pain accurately.

### Who will take informed consent? {26a}

Consent for the research team to approach potentially eligible participants will be facilitated by the clinical team. A research nurse will determine eligibility, provide study information, and obtain signed informed consent.

### Additional consent provisions for collection and use of participant data and biological specimens {26b}

N/A: No biological specimens were collected as part of this trial.

## Interventions

### Explanation for the choice of comparators {6b}

Currently, the provision of 24% sucrose prior to a heel lance is considered standard of care and will be used as a comparator to SSC.

Twenty-four per cent sucrose (0.1 ml) will be delivered by a research nurse experienced in NICU care, onto the anterior surface of the tongue, commencing 2 min prior to data collection, doses may be repeated every 2 min throughout the painful procedure as deemed necessary by the clinical care provider [40]. The only modification to usual practice will be to position the infant to ensure optimal data readings from the EEG net and to visualize their face on the video recording, to enable scoring of pain responses.

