### Strategies to improve adherence to interventions {11c}

Every effort will be made to ensure the fidelity of the intervention. Any deviation will be documented using an intervention fidelity checklist completed by the research nurse at the end of the procedure. Any need for additional (e.g. rescue) pain management strategies will be monitored and compared monthly across groups.

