#### Pain intensity

Pain intensity will be assessed using the Premature Infant Pain Profile—Revised (PIPP-R) [44, 45]. The original PIPP was developed by Stevens et al. in 1996 [46] and revised in 2012 [44]. The PIPP includes two physiological (heart rate, oxygen saturation), three behavioural (brow bulge, eye squeeze, nasolabial furrow), and two contextual (GA, behavioural state [BS]) variables known to modify pain responses. Each variable is scored on a four-point scale (0, 1, 2, 3) reflecting changes in magnitude from baseline values. GA and BS are reverse-scored to account for developmental and state differences in preterm and term infants abilities to respond to pain [46]. In the PIPP-R, the original seven variables of the PIPP are retained, but ordering and scoring of GA and BS has changed to ensure baseline characteristics prior to the painful event do not artificially inflate scores. The PIPP-R has demonstrated construct validation in infants of varying GAs during extreme group comparisons [44]. As facial actions are the most specific bio-behavioural indicator of acute procedural pain in newborn infants [47], the three individual facial actions within the PIPP-R will be analysed separately in addition to the composite PIPP-R score. Physiologic and behavioural data collection techniques, which have been developed and used extensively by this research team over the past decade, will be employed [48, 49]. For physiologic variables, heart rate and oxygen saturation will be measured continuously throughout the procedure via a pulse oximeter placed on the infant’s hand and recorded on the GES 400 EEG System 400 Physio 16 II. Behavioural state will be observed for 30 s prior to the noxious stimulus from video, and GA will be determined from the medical record. Time locking of the noxious-evoked stimulus and heel lance will be synchronized with EEG recordings, physiological data, and behavioural data using the time trigger device described previously. Electronic event markers will be used to synchronize all physiological and behavioural data, and to indicate four distinct phases of the standardized heel lance: (i) baseline data collection for 2 min; (ii) 2 min during and following sucrose administration; (iii) heel lance; and (iv) return to baseline for 2 min. Pain intensity will be calculated by trained coders, blinded to the study purpose and design, using newly developed facial coding software (Pain Assessment in Neonates, [PAiN]) developed recently by the Principal Investigator (PI) for previous research [38]. Inter-rater reliability of greater than 0.8 [50] with the trained coders for the PIPP-R scores will be established prior to data collection and monitored throughout the study using a random selection of infants after 20 infants are entered into the study. See Fig. 1 for overview of data collection procedures.

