#### Adverse events and safety monitoring

As the HydroCel Geodesic Sensor Net requires that electrode sponges are soaked in a warm saline solution prior to application to the infant scalp, a thermal cap will be placed over the sensor net during data collection to reduce heat loss. Infant axillary temperature will be monitored every 15 min throughout data collection to ensure normothermia (36.5 to 37.5 °C). Infants will be monitored constantly during data collection (observation and continuous cardiorespiratory and oxygen saturation recording) in order to prevent any risk of skin irritation while wearing the HydroCel Geodesic Sensor Net as well any incidence of choking, apnea (defined as unexplained cessation of breathing for 20 s or longer, or a shorter respiratory pause associated with bradycardia, cyanosis, pallor, and/or hypotonia [51]), or bradycardia (defined as a 30 beat per minute drop from baseline, or when the heart rate is below 100 beats per minute). Adverse events, need for a repeat heel lance to allow for sufficient blood collection, or administration of additional doses of “rescue” sucrose will also be recorded on the tolerance/adverse events section of the intervention fidelity checklist, which has been developed and validated in previous research by the PI [38].

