## Assignment of interventions: Blinding

### Who will be blinded {17a}

In keeping with clinical trials where interventions cannot be blinded, we will ensure that data will be collected independently from those conducting analysis (blinded to group allocation) to minimize bias. Mothers, staff, and research nurses and assistants completing data collection will not be blinded to whether the infant has been randomly assigned to SSC condition or the 24% oral sucrose condition. All individuals carrying out data analysis will be blinded to group assignment. Additionally, EEG data analysts will have no prior knowledge of study groups and assignment. Close up video of the infants face during the painful procedure with no sound will be recorded to ensure that coders will be blinded to all aspects of group allocation and study purpose.

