## Data collection and management

### Plans for assessment and collection of outcomes {18a}

Set-up of EEG equipment, video recording, and physiological monitoring is anticipated to take 20–30 min. Baseline measurements (BL1 and BL2, 2 min each), stabilization in SSC after transfer (15 min), and heel lance procedure (three to 5 min) is estimated to take 20–25 min for a total data collection period of 40–60 min. Infants will be followed until completion of a regularly scheduled heel lance procedure.

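### Rescue sucrose is listed as an adverse event although repeat sucrose belongs to the comparator's own regimen, so this item cannot support a safety claim for skin-to-skin contact

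*Protocol article*

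**What the plan says.** Under Hypotheses, Secondary, part (b) predicts fewer adverse events with SSC and spells out what counts. The list runs from choking, apnea, bradycardia and temperature instability to "need for repeat heel lance or “rescue sucrose” doses".

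Under Explanation for the choice of comparators {6b}, the sucrose arm gets an initial dose, and then "doses may be repeated every 2 min throughout the painful procedure as deemed necessary by the clinical care provider". The abstract describes the arms as infants who "receive (i) SSC plus sterile water and (ii) 24% oral sucrose". Intervention description {11a} gives the SSC arm no sucrose schedule.

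Adverse events and safety monitoring says that additional rescue doses "will also be recorded on the tolerance/adverse events section of the intervention fidelity checklist". Strategies to improve adherence {11c} adds: "Any need for additional (e.g. rescue) pain management strategies will be monitored and compared monthly across groups". On blinding, {17a} states: "Mothers, staff, and research nurses and assistants completing data collection will not be blinded".

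The statistical section on adverse events compares each safety outcome between arms by t-test. The section on pain intensity names a logistic model for binary adverse events. Neither defines a composite.

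**The concern.** One act, giving a further dose of sucrose because someone judges that the infant needs it, has two roles in the plan. In the comparator section it is allocated treatment. In the secondary hypothesis it is an adverse event, and one predicted to be rarer with SSC.

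Two things follow. First, the item differs in kind from the rest of the list: choking or apnea is harm, whereas another dose of the standard-of-care analgesic is a sign of insufficient pain relief. Second, only the sucrose arm has a regimen that provides for such doses, and they are given at the discretion of people who know the arm.

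At stake is the reading of hypothesis (b). A report of fewer adverse events with SSC that rested on this item could reflect need for analgesia, or the comparator's dosing rule, and say nothing about safety.

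**Working it through.** The plan gives no figure for rescue or repeat dosing, so there is nothing to reproduce. The check is a side-by-side reading.

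1. **Is rescue sucrose really in the adverse-event hypothesis?** Yes. It is named in the list attached to part (b), and the predicted direction is fewer with SSC.

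2. **Is repeat sucrose really part of the comparator's regimen?** Yes. {6b} allows it at 2 min intervals during the procedure, on the care provider's judgement of need.

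3. **Does the SSC arm have a matching provision?** No. It receives sterile water, and {11a} describes only the positioning. SSC infants may still receive rescue sucrose, since the monitoring text is not limited to one arm, but for them it would lie outside the allocated treatment.

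4. **Does the article separate a rescue dose from a permitted repeat?** No. The safety section speaks of additional rescue doses without saying whether regimen repeats are among them. The rule may be on the intervention fidelity checklist, which is not shown.

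5. **What follows under each counting rule?**
   - *Repeats counted:* treatment given as planned in the sucrose arm enters the adverse-event tally, and the item leans towards SSC.
   - *Repeats not counted:* that route to a result favouring SSC is closed. Any lean would be against SSC, because some further doses in the sucrose arm would be exempt.

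6. **What holds under both rules?** The item measures judged need for analgesia, decided by unblinded staff. It does not measure harm.

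7. **How far does it reach?** Safety outcomes are compared one by one, so the other listed events are not contaminated. Repeat heel lance is tied to obtaining enough blood, which is defined alike in both arms.

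**The case against.** The strongest reply is that the article never says regimen repeats are recorded as rescue. It uses a distinct term, and the counting rule could sit on a checklist developed in earlier work. That stands: the lean towards SSC is conditional, and a reader who infers that planned doses are certainly logged as adverse events goes beyond the text.

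A reader might also infer that the item is skewed whatever the checklist says, because with repeats excluded only SSC infants could register an event. The documents do not support this. The regimen has a stated volume, interval and period. A dose given sooner, in a larger amount or after the procedure would fall outside it and could count as rescue in the sucrose arm. The two counting rules also lean in opposite directions.

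A third temptation is to count permitted doses, or to ask how few would make the comparison significant. The timing is not fixed well enough. {6b} times the first dose from the start of data collection. The link to the lance has to be pieced together from the phases under Pain intensity ("2 min during and following sucrose administration; (iii) heel lance") and the duration in {18a} ("heel lance procedure (three to 5 min"). Permitted doses are also not given doses. Significance cut-offs would apply to any binary item at 63 per arm and would change with the test chosen.

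Finally, it can be said that sucrose beyond the first treatment, counted in both arms, is a coherent measure of unmet analgesic need, and that the fix below counts much the same thing under another name. That is fair, but the name decides which conclusion the trial may draw. As an adverse event the item feeds a safety claim; as analgesic use it does not.

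**Conclusion.** The concern holds as a minor point about classification. Rescue sucrose should not be among the adverse events predicted to be fewer with SSC. A further dose shows need for analgesia, and repeat dosing at the discretion of unblinded staff is built into one arm only.

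If permitted repeats are logged as additional doses, comparator treatment given as planned is scored as an adverse event in SSC's favour. Whether that happens is unknown without the checklist, and its size cannot be estimated without a rate of repeat dosing.

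The scope is one item of secondary hypothesis (b). Choking, apnea, bradycardia, temperature instability and repeat heel lance are unaffected, as are the primary event-related potential, the PIPP-R and the sample size.

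**What to change.** - Remove rescue sucrose from the adverse-event list in secondary hypothesis (b). Repeat heel lance may stay as a separately analysed item.
- Report sucrose use as its own analgesic-use outcome, counting every sucrose dose after the start of the lance in the same way in both arms.
- Use the same rule for the monthly comparison in {11c}.
- State that a difference reflects analgesic use under unblinded dosing that depends on the regimen, and is not evidence on safety.

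The cost is a slightly narrower hypothesis (b) and a small change of wording. Additional doses already go on the fidelity checklist. If it does not currently log regimen repeats, or place doses relative to the lance, one line must be added. Care and sample size do not change.
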